### Health economic evaluation

The health economic evaluation will follow the Consolidated Health Economic Evaluation Reporting Standards 2022 Statement [17] and will include a series of cost-utility analyses using cost per quality adjusted life years (QALYs) gained for children (using SDQ scores mapped onto a multi-attribute utility instrument using published algorithms), for caregivers (using the scores from the AQOL-8D) and for the dyad as the outcome. Costs will be analyzed from two perspectives: a healthcare system perspective (the Portuguese National Health Service; SNS) and a broader societal perspective. The healthcare system perspective includes the cost to run the intervention, collected from project documentation. The broader societal perspective includes, in addition to intervention costs, other healthcare costs (healthcare utilization and medication), as well as costs beyond healthcare, including social services, transportation, out-of-pocket expenses, and productivity losses related to absenteeism and presenteeism from paid and unpaid work. Total costs and QALYs will be aggregated over the trial period and estimated using the area under the curve approach [20]. Differences in total QALYs and costs for children and caregivers will be analyzed using regression models. Incremental cost-effectiveness ratios (ICER) will be estimated as the ratio between the difference in costs and the difference in QALYs for children, caregivers and the dyad for each costing perspective. Uncertainty around the cost and QALY estimates will be explored using non-parametric bootstrapping and plotted on cost effectiveness planes [11]. The probability of cost-effectiveness of the intervention at different values of willingness to pay will be represented visually as cost-effectiveness acceptability curves [9].

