### Objectives and hypotheses

The primary objective of the current project is to examine the effect of the VIPP-SD on parental sensitivity and sensitive discipline of the target parent, from baseline to 8 weeks after and 6 months after the intervention. We expect a statistically significant increase in sensitivity and sensitive discipline among parents from the intervention condition (VIPP-SD) when compared with parents from control condition ("dummy" contacts with interveners) from pre- to post-intervention.The secondary aim of the study is to examine the value of the intervention in reducing children’s behavioral problems, as a function of increased parental sensitivity and the use of sensitive discipline strategies. It is expected that improvements in parental sensitivity and sensitive discipline resulting from the VIPP-SD intervention will be associated with lower levels of behavioral difficulties in intervention group children when compared with children from control condition ("dummy" contacts with interveners) from pre- to post-intervention and follow-up intervention.A third objective is to evaluate the effects of the VIPP-SD on parent-reported parenting practices, parental anxiety and depression symptoms, and parental health related quality of life. We expect that parents in the intervention condition will report a decrease in depression and anxiety symptoms, as well as more nurturing and less restrictive parenting practices from pre- to post-intervention and 6-months follow-up.The fourth objective is to examine the cost-effectiveness of the intervention by assessing the differential impact of the intervention compared to the control on quality adjusted life years (QALY) and resource use and related costs. We expect that VIPP-SD leads to improved health related quality of life (HRQoL) and a reduction in the use of societal resources compared to the control condition.

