#### Resource use

Resources used by children and their parents will be measured using a questionnaire adapted from published questionnaires [26]. Resource use will include healthcare services (accident and emergency visits, primary care and specialized outpatient visits and inpatient stays, medication), social services, transportation, absenteeism and presenteeism from both paid and unpaid work, and out-of-pocket expenses. This measure will be used for economic evaluation.

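### The SNS perspective is defined by intervention running cost alone, so its cost-utility results cannot respond to differences in SNS-borne care

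*Protocol article*

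**What the plan says.** All of this is in the protocol article. The Health economic evaluation section sets up two cost analyses: "Costs will be analyzed from two perspectives: a healthcare system perspective (the Portuguese National Health Service; SNS) and a broader societal perspective". It then gives the content of each. For the first: "The healthcare system perspective includes the cost to run the intervention, collected from project documentation". For the second: "The broader societal perspective includes, in addition to intervention costs, other healthcare costs (healthcare utilization and medication), as well as costs beyond healthcare", followed by a list covering social services, travel, families' own payments and lost productivity.

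An ICER is planned as "the ratio between the difference in costs and the difference in QALYs for children, caregivers and the dyad for each costing perspective". Bootstrapping, cost-effectiveness planes and acceptability curves are to describe the uncertainty.

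The Resource use section shows that the relevant data will be gathered: "Resource use will include healthcare services (accident and emergency visits, primary care and specialized outpatient visits and inpatient stays, medication". It adds: "This measure will be used for economic evaluation". No other section places healthcare use or medicines in the SNS perspective.

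The economic hypothesis, under Objectives and hypotheses, reads: "We expect that VIPP-SD leads to improved health related quality of life (HRQoL) and a reduction in the use of societal resources", relative to control.

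**The concern.** A payer perspective should carry the costs that fall on that payer. To the extent that the SNS funds emergency visits, primary care, outpatient visits, hospital stays and medicines, these belong in an analysis named after it. The article calls them healthcare costs and separates them from costs outside healthcare, yet places them outside the healthcare-system perspective.

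At stake is how one of the two planned perspectives is read. The introduction argues that prevention may save health and social expenditure, and the stated aim is to inform health policy decision-makers. A reader given an SNS cost per QALY would take it to be net of changes in SNS care. Under the written definition it would be a programme cost per QALY with an SNS label.

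**Working it through.** The article gives no unit cost, cost difference, QALY difference or ICER, so there is no figure of its own to reproduce on this point. The check is of the definitions, then of the algebra.

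**1. Content of each perspective as written (Health economic evaluation)**

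| Cost item | SNS | Societal |
|---|---|---|
| Running the intervention | listed | listed |
| Healthcare use | not listed | listed |
| Medicines | not listed | listed |
| Social services, travel, families' own payments, productivity | not listed | listed |

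Two features of the text suggest that the SNS entry is the whole list.
- The societal sentence starts from intervention costs alone and adds healthcare use to them. Had healthcare use already been in the SNS perspective, the additions would start with costs outside healthcare.
- The named source for the SNS perspective is project documentation. Families' use of services comes from a different source, the resource-use questionnaire.

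**2. Algebra**

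Let ΔC be a mean cost difference (VIPP-SD minus control) and ΔQ the mean QALY difference.

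- As written: ΔC(SNS) = ΔC(delivery).
- With SNS-borne care counted: ΔC(SNS) = ΔC(delivery) + ΔC(healthcare use) + ΔC(medicines).
- In both cases: ICER(SNS) = ΔC(SNS) / ΔQ.

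The care terms are absent from the first expression. Any rise or fall in SNS-borne care therefore leaves the SNS incremental cost unchanged, and with it the cost axis of the plane and the cost input to the acceptability curve.

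**3. Sign of the SNS increment**

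ΔC(delivery) is the cost of delivering VIPP-SD minus the cost of the control contacts, or minus zero if those are not costed. The Study design section describes the control contacts as phone calls made as often as the intervention sessions. If VIPP-SD delivery costs more, ΔC(SNS) is positive and a saving cannot appear, whatever happens to care.

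**4. Illustration (all euro and QALY figures are assumptions, not trial values)**

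Take ΔC(delivery) = EUR 1,000 and ΔQ = 0.02. As written, the SNS ICER is 1,000 / 0.02 = EUR 50,000 per QALY in every row.

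| Assumed difference in SNS-borne care (EUR) | ΔC(SNS) with care counted (EUR) | ICER with care counted |
|---|---|---|
| +200 | 1,200 | 1,200 / 0.02 = 60,000 |
| 0 | 1,000 | 1,000 / 0.02 = 50,000 |
| -500 | 500 | 500 / 0.02 = 25,000 |
| -1,000 | 0 | 0 |
| -2,000 | -1,000 | cost-saving |

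Varying the assumed delivery difference from EUR 500 to 1,500 moves the as-written ICER from 500 / 0.02 = 25,000 to 1,500 / 0.02 = 75,000, still with no response to care. Over the same range, with care from +200 to -2,000, the full SNS increment runs from 1,500 + 200 = +1,700 (1,700 / 0.02 = EUR 85,000 per QALY) to 500 - 2,000 = -1,500 (cost-saving). The spread reflects only the chosen inputs. It shows that the error has no fixed direction.

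**5. Reach**

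Two perspectives and three outcome units (child, caregiver, dyad) give 2 × 3 = 6 ICERs. The three SNS ones are affected and the three societal ones are not.

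**The case against.** **The exclusion is inferred.** The text says that the SNS perspective includes the running cost, not that it is limited to it, and a journal article condenses a fuller plan. A clause may simply have been misplaced. This stands in part: one cannot say that a wrong analysis will be carried out. But the article does state the content of both perspectives, the next sentence supports the narrow reading, and nothing corrects it. If healthcare use was meant for both perspectives, the wording still needs to change.

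**The fourth objective is still tested.** A reader might infer that the trial cannot detect the cost offsets it hypothesises. The article does not support that. The hypothesis concerns societal resources, and the societal analysis counts healthcare use, medicines and the wider items. This objection stands in full.

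**Savings are not ruled out by construction.** A reader might infer that an SNS saving is impossible in all circumstances. That needs delivery of VIPP-SD to cost more than the control calls. This is likely for video-feedback sessions recorded at home against phone calls, but the article gives no costs and does not say whether the calls are costed. The claim is conditional.

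**The omitted care may not dominate cost uncertainty.** It is tempting to call it the main source. The article has no cost variances, so that cannot be claimed.

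**The remedy is not purely a relabelling.** The Resource use section lists types of service and families' own payments, but does not say that the payer of each visit or medicine is recorded. This stands, and the fix allows for it.

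**Conclusion.** The definition is defective as written. The SNS perspective carries only intervention running cost, while healthcare use and medicines are placed in the societal perspective alone. The SNS incremental cost, ICERs, plane and acceptability curve therefore do not respond to between-arm differences in SNS-borne care. The bias can favour either arm. The statement that no saving can appear rests on the assumption that VIPP-SD delivery costs more than the control contacts.

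The size cannot be computed from the article. The conclusion assumes that the SNS bears at least part of the care that families will report. The defect is confined to one of two costing perspectives within the fourth objective. The societal ICERs, the sample size and the parenting and child-behaviour analyses are untouched.

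**What to change.** Rewrite the two definitions in the protocol or economic analysis plan:

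- **SNS perspective:** intervention cost, plus healthcare use and medicines borne by the SNS, taken from the resource-use questionnaire. State how SNS-borne costs are separated from families' own or other private costs, for example by applying SNS unit costs to reported use.
- **Societal perspective:** the SNS costs, plus social services, travel, families' own payments and productivity losses. The separation rule should also ensure that a privately paid visit is not counted twice.
- **Delivery-only result:** if it is kept, report it separately as programme cost per QALY.

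The cost is mainly wording, because service use and medicines are already to be collected. The one substantive addition is the costing rule for who pays, since the article does not say that the questionnaire records this. If it does not, either a payer item is added or the assumption is stated. The change should be made before any cost data are analysed, so that the choice of cost items cannot appear to follow the results.

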### Study design

To evaluate the intervention’s effectiveness, we will conduct a two-arm randomized controlled trial (RCT) in which participating families will be randomly assigned to either an intervention group or a control group ("dummy" contacts with interveners) after the baseline visit. Parents in the Control Group will receive, at the same frequency as the Intervention Group’s sessions, a phone call addressing topics related to child development (e.g., sleep, nutrition, etc., but not providing feedback on parenting). The protocols will be specifically designed to encourage participants to talk about their children. Randomization will be performed using a computer-generated random allocation sequence, stratified by child age and sex to ensure balanced group characteristics and group assignment will be done after the baseline assessment is completed to minimize potential bias (Fig. 1).

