### Instruments

Data collection for sociodemographic variables will take place at baseline (pretest). Parental sensitivity and sensitive discipline will be coded from videotaped mother–child interactions by independent, trained observers who are blinded to intervention conditions; these measures will be collected at baseline and immediately post-intervention (posttest). All other measures will be collected at three time points: baseline, posttest, and follow-up. Due to time and personnel limitations, the follow-up evaluation will rely solely on questionnaires.

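### As worded, the area-under-the-curve rule covers total costs as well as QALYs; if resource use is recalled over contiguous periods, it mis-weights posttest against follow-up in the incremental cost

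*Protocol article*

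**What the plan says.** The protocol article gives one estimation rule for both parts of the cost-effectiveness ratio (Health economic evaluation): "Total costs and QALYs will be aggregated over the trial period and estimated using the area under the curve approach".

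The surrounding facts are these:

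- **Measurement times.** Under Instruments, everything except the observed parenting measures and the sociodemographic data follows one schedule: "All other measures will be collected at three time points: baseline, posttest, and follow-up". Resource use and the AQOL-8D fall under this.
- **What is measured.** Under Resource use: "Resources used by children and their parents will be measured using a questionnaire adapted from published questionnaires". The items are counts and amounts, namely "Resource use will include healthcare services (accident and emergency visits, primary care and specialized outpatient visits and inpatient stays, medication"), together with social services, transport, lost work and out-of-pocket spending. No recall window is given.
- **Allocation.** Under Study design, "group assignment will be done after the baseline assessment is completed to minimize potential bias". A backward-looking baseline report therefore describes the time before randomisation.
- **Intervention cost.** "The healthcare system perspective includes the cost to run the intervention, collected from project documentation". It does not come from the repeated questionnaire.
- **Societal perspective.** "The broader societal perspective includes, in addition to intervention costs, other healthcare costs (healthcare utilization and medication"), plus costs outside healthcare. This is where the questionnaire-based costs enter.

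**The concern.** A utility is a level at a point in time. Joining the measured levels and integrating over time gives QALYs, and the baseline value belongs in that calculation. Visits, inpatient days and lost work are amounts that build up between questionnaires. If a report already holds the amount for its period, the period amounts should be added.

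A trapezoid treats each report as the rate at the visit and spreads it half backward and half forward. The baseline report is carried forward into the trial period, the posttest report is carried into follow-up time it did not observe, and the last report loses half of the interval it did observe.

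The incremental cost is the numerator of the ICERs and feeds the cost-effectiveness planes and acceptability curves. The fourth objective expects lower use of societal resources, and the article's background says that effects on child behaviour may emerge over time. Late savings are the ones this rule would shrink most.

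**Working it through.** The article states no cost, QALY or ICER figure, so there is none to reproduce. The check compares the two rules on the same cost reports.

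**Inputs**

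- Three reports, at times 0, t1 and t2 (Instruments).
- Timing: the primary objective speaks of change "from baseline to 8 weeks after and 6 months after the intervention", while Instruments places the observed posttest immediately after the intervention. The intervals are therefore assumptions: 8 weeks to posttest and 26 more to follow-up (t1 = 8, t2 = 34), with alternatives below.
- Recall: assumed contiguous, so each report covers the whole time since the previous one. The article does not state this.
- c0, c1, c2: mean weekly cost in the period before each report.

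**Formulas**

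- Sum of period costs = t1·c1 + (t2 − t1)·c2
- Trapezoid = (t1/2)·c0 + (t2/2)·c1 + ((t2 − t1)/2)·c2

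**Weights in weeks on c0 / c1 / c2 at t1 = 8, t2 = 34**

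- Sum: 0 / 8 / 26
- Trapezoid: 4 / 17 / 13

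The baseline report takes 4/34 = 11.8% of the weight. The follow-up report keeps 13/26 = 50% of its own. The posttest report gets 17/8 = 2.1 times its own.

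**Effect on the incremental cost at t1 = 8, t2 = 34**, with no expected difference at baseline and illustrative savings in money units per week:

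- Constant saving of 10: sum −340, trapezoid −300, ratio 0.88
- Growing saving, 5 then 15: sum −430, trapezoid −280, ratio 0.65
- Saving of 10 in follow-up only: sum −260, trapezoid −130, ratio 0.50
- Saving of 10 before posttest only: sum −80, trapezoid −170, ratio 2.13

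**Ratios under other assumed timings**

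| t1, t2 (weeks) | constant | growing | follow-up only | before posttest only |
|---|---|---|---|---|
| 4, 30 | 0.93 | 0.66 | 0.50 | 3.75 |
| 6, 32 | 0.91 | 0.65 | 0.50 | 2.67 |
| 8, 26 | 0.85 | 0.65 | 0.50 | 1.63 |
| 12, 38 | 0.84 | 0.64 | 0.50 | 1.58 |

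**Role of the baseline report.** Its expected difference between arms is zero, so the term (t1/2)·c0 drops out of the expected incremental cost. A simulation of 5,000 trials with 60 families per arm and a follow-up-only saving of 10 per week gave mean differences of −258 (sum) and −131 (trapezoid), close to −260 and −130 from the weights alone. The bias comes from the reweighting of posttest against follow-up. Baseline cost raises both arms' totals and brings chance imbalance with it.

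**Opposite case: short recall.** Suppose each questionnaire covers only a short window, so that it reports a rate near the visit, and the difference in rates moves linearly between visits.

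- Difference of 0, −10, −10 at the three visits: true −300, trapezoid −300, carrying each rate back over its interval −340.
- Difference of 0, −5, −15: true −280, trapezoid −280, carry-back −430.

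Here the trapezoid is exact, and scaling each report back over the whole interval is the biased choice.

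**The case against.** The strongest reply is that the error depends on something the article does not state. With short, fixed recall windows the reports are rates, the gaps must be filled somehow, and AUC is a legitimate way to fill them. AUC also returns money only if costs enter as rates, so the wording may reflect a rate-based method. The recall window may be set out in a fuller plan, and its absence from an article is no finding. All of this stands and makes the point conditional. It does not remove it: the sentence names an estimator for costs without tying it to the condition that would justify it, and infrequent, lumpy items such as inpatient stays fit linear interpolation poorly.

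A second reply is that the sentence compresses two steps, with costs and QALYs aggregated and AUC meant for QALYs only. That reading is possible, but the grammar gives both subjects both verbs. If it is what the sponsor means, splitting the sentence costs nothing.

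Three stronger readings are tempting and are not supported:

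- *Pre-randomisation spending biases the incremental cost.* It does not in expectation, because allocation follows baseline.
- *The cost of delivering VIPP-SD is counted about twice.* It comes from project documentation, and nothing places it in the posttest report. The healthcare perspective, as the article describes it, therefore need not be affected.
- *Every societal ICER is wrong.* That would need contiguous recall, which is not stated. Even then the size and direction depend on when costs diverge: a constant saving is understated modestly, and an early difference is overstated.

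**Conclusion.** The point holds in conditional form. The stated rule applies a QALY estimator to accrued costs. If the questionnaires recall contiguous periods and all three enter a trapezoid, the incremental questionnaire-based cost is mis-weighted. At 8 and 34 weeks the ratio to the true value is 0.88 for a constant saving, 0.65 for the growing saving, 0.50 for a saving only in follow-up and 2.1 for a difference only before posttest. Over the timings tried, the constant case runs from 0.84 to 0.93, the growing case from 0.64 to 0.66 and the early-only case from 1.58 to 3.75. The follow-up-only figure stays at 0.50 whatever the timing.

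What is exposed is the questionnaire-based part of societal cost and the ICERs, planes and acceptability curves built on it. The observed and self-reported outcome comparisons are untouched, and AUC remains right for QALYs. This concerns the fourth objective, and is worth correcting before analysis because the correction is so cheap.

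**What to change.** Replace the single sentence with a split rule, for example:

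> QALYs will be estimated using the area under the curve approach. Questionnaire-based costs will be summed over the post-randomisation periods covered by the posttest and follow-up reports; only where a recall window is shorter than the interval will weekly cost rates be interpolated across the uncovered time. Intervention cost is added once from project documentation. Baseline cost is not part of the total and is used only as a regression covariate (and, where rates are interpolated, as the starting rate).

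The interpolation clause matters: with short windows, a plain sum would leave out the unrecalled weeks, and scaling each report up to its full interval can mislead when cost rates trend.

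The cost is slightly more analysis work, and the recall window of each questionnaire must be stated. No extra visits or participants are needed.
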